### Data management

All investigators, including doctors, nurses, and research associates, attended a training workshop before the trial commenced to ensure the accuracy of both outcome assessments and data collection. All investigators were provided with a protocol and standard operating procedures. All data were collected in the standard general reporting format and recorded in the electronic data acquisition system (the CRIP system of the Shanghai Shenkang Hospital Development Center). The Shanghai Shenkang Hospital Development Center and the Shanghai Changzheng Hospital appointed data inspectors to regularly check the authenticity, accuracy, and integrity of the data to ensure the quality of the data collected.

### Statistical analysis methods

The data were analyzed using the R (v.2.1.1) tool. The measurement data were statistically presented in terms of mean ± standard deviation, maximum, minimum, mean 95% confidence interval, and median. A *t*-test was used for intergroup comparisons of data conforming to normality and homogeneity of variance, while a nonparametric test (chi-square test) was used for intergroup comparisons of data that did not conform to normality. The enumeration data were statistically represented by frequency (composition ratio). A rank–sum test was used for ordinal categorical variables, and the chi-square test was used for nominal categorical variables. Two-tailed tests were used for all statistical analyses, and a *P*-value of less than or equal to 0.05 was considered statistically significant for the tested difference.

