##### Determination of endometrial cell proliferation

To determine whether the ECM could promote endometrial cell proliferation, Ki67 immunohistochemical staining was conducted. Von Willebrand factor immunohistochemical staining in the endometrial injury region was conducted to observe the regeneration and distribution of microvessels in the endometrium. At a magnification of ×40, the proliferative cell count of three fields was randomly selected and averaged.

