### Secondary outcome measures

These included the endometrial thickness, menstrual volume, and clinical pregnancy rate.“Endometrial thickness” referred to the anterior and posterior diameter of the endometrium in the longitudinal section of the uterus, which changed with the menstrual cycle. The measurement of endometrial thickness was based on the following: In the median sagittal section of the uterine body, perpendicular to the midline of the endometrium, the maximum thickness diameter was measured between the lateral edges of the double-layer endometrium. If there was uterine effusion, the thickness and diameter of the two monolayers were measured and added to the overall total.The evaluation of menstrual volume is the total amount of bleeding in each menstrual cycle. The normal menstrual volume is 20–60 ml, and more than 80 ml is considered to be excessive. Typically, this is judged by the number of sanitary napkins used. Under normal circumstances, 10–20 sanitary napkins will be used in a menstrual cycle. If the level of menstruation required fewer than 10 sanitary napkins or only one was needed, the amount of menstruation had been reduced. Based on the number of sanitary napkins that were used before the hysteroscopy, if this was more than the amount before the procedure, the amount of menstruation was considered to have increased. If there was no change in the menstrual volume compared with before the procedure, the menstrual volume was considered as having shown no improvement.Blood β-hCG and progesterone were measured 14 days after embryo transfer to evaluate whether a biochemical pregnancy was present. On day 35 after embryo transfer, a vaginal ultrasound showed that there was a gestational sac in the uterus with an embryo and fetal heart beat; this was determined as a clinical pregnancy.Ongoing pregnancy rate = the number of clinical pregnancies ≥12 weeks/the number of embryo transfer cycles × 100%Clinical pregnancy rate = the number of clinical pregnancies/the number of embryo transfer cycles × 100%Embryo implantation rate = the total number of implanted embryos/the total number of transplanted embryos × 100%Ectopic pregnancy rate = the number of ectopic pregnancies/the total number of clinical pregnancies × 100%Early spontaneous abortion rate = the number of spontaneous abortions at a gestational age of <12 weeks/the total number of clinical pregnancies × 100%

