### Safety evaluation indexes

The safety evaluation indexes included postoperative intrauterine infection (fever, abnormal vaginal discharge), the duration of vaginal bleeding, lower abdominal pain (Visual Analogue Scale/Score, VAS pain score), and allergic reactions. VAS is a commonly used scoring standard for evaluating pain intensity in the clinic. This method is classified according to the impact of pain on patients’ sleep. If pain symptoms do not affect patients’ sleep, patients belong to mild pain. If the pain symptoms will affect the patient’s sleep, but the patient can still fall asleep, the patient belongs to moderate pain. If the pain symptoms make the patient unable to sleep, the patient belongs to severe pain symptoms. Patients will be asked about the degree of pain 2–3 days after hysteroscopy.

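### The plan names the chi-square test for continuous data that fail normality; as written that test cannot compare continuous values, though the primary outcome is unaffected

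*Protocol article*

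**What the plan says.** All the test rules stand in the protocol article under Statistical analysis methods, in this order.

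- **Continuous data, summary:** "The measurement data were statistically presented in terms of mean ± standard deviation, maximum, minimum, mean 95% confidence interval, and median".
- **Continuous data, parametric branch:** the t-"test was used for intergroup comparisons of data conforming to normality and homogeneity of variance".
- **Continuous data, other branch:** "while a nonparametric test (chi-square test) was used for intergroup comparisons of data that did not conform to normality".
- **Categorical data:** after a sentence on how counts are summarised, the rank-sum "test was used for ordinal categorical variables, and the chi-square test was used for nominal categorical variables".

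The chi-square test is thus named twice, once for non-normal continuous data and once for nominal data. The rank-sum test is named once, for ordinal categories only. The section gives no cut-points, median split or other categorisation for continuous outcomes.

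The variables that the rule could govern are described elsewhere:

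- Of the secondary outcomes, "These included the endometrial thickness, menstrual volume, and clinical pregnancy rate", thickness is a measured length.
- The Safety evaluation indexes include "the duration of vaginal bleeding, lower abdominal pain".
- Under Determination of endometrial cell proliferation, "the proliferative cell count of three fields was randomly selected and averaged".
- Intrauterine volume and the flow and vascularization indices are recorded at screening and around embryo transfer.

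**The concern.** A test of counts has been assigned to data that are not counts in categories. An analyst holding a non-normal continuous outcome has three ways to proceed, and none is satisfactory:

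1. Apply chi-square to the raw values, which gives a result that carries no information about the group difference.
2. Choose cut-points to make categories. The plan fixes none, so the choice could be made with the data in view.
3. Ignore the sentence and use a rank test, which departs from the published plan.

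At stake is the validity and pre-specification of the continuous secondary, safety and exploratory comparisons.

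**Working it through.** No figure in the article depends on this sentence, so there is nothing of the plan's own to reproduce. The check has three parts.

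**1. Which data the sentence governs.** The clause follows the summary of measurement data by mean, standard deviation and median, and it is the alternative to the t-test. Categorical data come only afterwards. So the chi-square clause is about continuous data, and it cannot be read as an early mention of the nominal rule.

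**2. What chi-square does on untied continuous values.** Input: 83 per arm (Sample size section), so N = 166 distinct values and a 2 × 166 table.

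- Each column holds one participant. The expected count in each cell is 1 × 83/166 = 0.5.
- Each observed count is 0 or 1, so each cell contributes (0.5)²/0.5 = 0.5.
- There are 2 × 166 = 332 cells, so chi-square = 332 × 0.5 = 166.
- Degrees of freedom = (2 − 1) × (166 − 1) = 165.
- The p-value is 0.46.

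The values themselves never enter the calculation, so the answer is the same whether the arms are identical or do not overlap at all. With the 100 per arm to be enrolled, the same algebra gives 200 on 199 degrees of freedom, p = 0.47. Ties from rounding would change the exact figure. The cells would still be sparse unless the values were grouped coarsely, and the test would still ignore their order.

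**3. What happens if categories are made.** The plan gives none, so everything here is assumed: a split at the pooled median, 83 per arm, two-sided 0.05, and the distributions and effects shown. The figures are simulated power.

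| Assumed data | Rank-sum | Median-split chi-square (uncorrected) |
|---|---|---|
| Log-normal, shift about 0.44 log-SD | about 78% | about 65% |
| Gamma, shape 2, scale ratio 1.33 | 66% | 52% |
| Double-exponential, scale 1, shift 0.5 | 77% | about 83% |

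Repeat runs moved the log-normal figures by about a point either way. Under a normal shift the large-sample efficiency of the median split relative to the rank-sum test is (2/π)/(3/π) = 0.637/0.955 = 0.67. Under a double-exponential shift the efficiencies against the t-test are 2 for the median test and 1.5 for the rank-sum test, so the order reverses, as in the last row.

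Part 2 shows that the rule fails as written. Part 3 shows only that the result depends on choices the plan does not make.

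**The case against.** **It is probably a drafting slip.** The sentence says that a nonparametric test is intended, and the rank-sum test appears shortly afterwards in the same section. That is plausible, but intent cannot be established from the text, and nothing elsewhere in the article corrects it. Nor can it be left to an analysis plan: a specific unsuitable test is named, so a sound analysis plan would have to contradict the article.

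**The reach is narrow.** This stands, and it lowers the severity.

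- A reader might infer that the trial's main conclusion is at risk. The documents do not support that. The primary outcome is a response rate, a proportion for which chi-square is suitable, and the sample size rests on that rate alone.
- A reader might also infer that all the secondary outcomes are affected. Clinical pregnancy is a proportion. Menstrual volume is judged from sanitary napkin use as increased or not improved, so the rule would govern it only if it were analysed as an amount. Endometrial thickness is the one named secondary outcome that is clearly continuous.
- The ultrasound and tissue measurements are taken, but they are not listed among the primary and secondary outcomes.

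**Non-normality is not documented.** This also stands. The article gives no distribution for any variable, so how often the faulty branch would be used is unknown. Durations and averaged counts are often skewed, but that is an expectation and not a figure from the plan.

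**The power loss is not a trial figure.** This stands too. A reader might infer that chi-square always costs about 13 points of power here. The median split, the distributions and the shifts are all assumed, and the double-exponential case goes the other way.

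**Conclusion.** Wrong as written; moderate severity. The article assigns the chi-square test to continuous data that fail normality and gives no categorisation to make it usable. On untied values at 83 per arm the result is fixed at 166 on 165 degrees of freedom, p = 0.46, and no shift can be detected. That conclusion needs no assumption about effect size or distribution, only that the values are untied.

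The consequence is conditional. It applies to endometrial thickness, bleeding duration and the ultrasound and tissue measurements, each only if it fails the normality condition. The power figures are illustrations and are not a measure of harm to this trial.

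**What to change.** Replace the clause so that measurement data that do not conform to normality are compared with the Wilcoxon rank-sum (Mann–Whitney) test, and keep the chi-square test for nominal variables only. A Hodges–Lehmann shift with a 95% confidence interval would be a useful but optional addition; it is not needed to correct the error.

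The same sentence also leaves data that are normal but have unequal variances without a test, and the revision could settle that as well.

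The cost is one sentence. It needs no new data and no change to the sample size or the primary analysis. It should be made, and recorded as a correction, before the groups are compared.

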Endometrial injury can easily cause IUA, which primarily manifests as an endometrial basal layer injury caused by trauma, infection, and other factors, resulting in the dysfunction of functional endometrial repair; in turn, this will lead to the proliferation of fibrous connective tissue and endometrial fibrosis as well as partial or total intrauterine occlusion [2, 4]. According to the consensus of Chinese experts on the clinical diagnosis and treatment of intrauterine adhesions [5], at present, for patients suffering from infertility, recurrent abortion, and oligomenorrhea and for those with special fertility requirements, transcervical resection of adhesion (TCRA) can be conducted as a preferred treatment (recommendation level: C). Moreover, TCRA combined with an intrauterine device (IUD), Foley balloon support, or estrogen and progesterone replacement therapy has shown degrees of anti-adhesion value, although their effects are variable. An IUD placement after moderate and severe IUA could reduce the formation rate of re-adhesion to 35% [6] (evidence level: I). But meta-analysis showed that the menstrual improvement rate ranged between 28.5 and 100%. Several studies have indicated significant differences in this regard [7]. In addition, although an intrauterine balloon can make the total effective rate of IUA repair reach 71.67% [8] and improve the menstrual rate up to 81.4–95% [9, 10], the shape of the balloon used in clinics is not suitable for the intrauterine cavity, which makes it difficult to block the wound completely. Moreover, if the intrauterine balloon is not placed properly, intimal ischemia and necrosis may occur, which will impact intimal regeneration and repair. In particular, for patients with severe IUA, due to endometrial basal layer damage, reduced residual normal endometrial tissue, and poor regeneration ability, the recurrence rate of postoperative adhesion can still be as high as 62.5%, while the success rate of pregnancy will range between only 22.5 and 33.3% [11]. Therefore, establishing an anti-adhesion method that can promote the repair of endometrial injury is of great significance.

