### Randomization and allocation

Eligible participants will be randomly assigned to the experimental group or the control group in a 1:1 ratio by central randomization performed by an independent statistician from our team. Random numbers are generated by Excel, which will generate a random number table, and the allocation sequence was registered on the Shanghai Shenkang Development Center (https://crip-ec.shdc.org.cn/html/admin/auth/login). According to the random number table, the statistician puts each grouping scheme into an opaque envelope, writes the code on the outside of the envelope, seals it, and gives it to the researcher. Once the hysteroscopic process entered the uterine cavity, the degree of uterine cavity adhesion was evaluated according to AFS. If the uterine cavity was assessed as reflecting moderate or severe uterine cavity adhesion, the itinerant nurse opened the envelope with the corresponding number. Then, the operator intervened according to the grouping scheme in the envelope. The process of unpacking the envelope was time consuming but did not affect anesthesia or hysteroscopy. The researchers were made aware of the distribution following the hysteroscopic surgery.

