### Sample size

The sample size calculation is based on the repair rate of moderate/severe IUA. Based on the fact that the repair rate of Foley balloon placement was 47–71.67% [8, 19], we assume that the effective rate of uterine adhesion repair can reach 80%. According to the calculation method for several cases related to the superiority study, the number of samples was estimated as 83, with *α* = 0.025 (one-sided) and *β* = 0.2. A sample size of 83 prospectively enrolled participants in each randomization arm. In consideration of a dropout rate of 20%, we will enroll 100 participants in each group response.

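### The primary comparison could be stratified by baseline AFS severity: the unadjusted chi-square test is valid, but it gives up some power and leaves the estimate open to chance imbalance in severity

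*Protocol article*

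**What the plan says.** All references are to the protocol article.

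- **Timing of the severity score.** Under Randomization and allocation, once the hysteroscope is in the cavity "the degree of uterine cavity adhesion was evaluated according to AFS". Only if the result is moderate or severe does the nurse open the envelope. Severity is therefore a true pre-randomisation variable.
- **Sequence.** The same section says "Random numbers are generated by Excel, which will generate a random number table". Allocation is 1:1, and no stratification factor is named.
- **Severity classes.** Table 1 puts moderate disease at 5–8 points and severe at 9–12.
- **Primary outcome.** Primary outcome measures defines effective repair as a fall of at least 4 points in total AFS score. The response rate is responders divided by the number in the group.
- **Tests.** Statistical analysis methods lists tests by type of data: t-test, rank-sum, and "the chi-square test was used for nominal categorical variables". No covariate or stratum appears. The section does not say which test belongs to the primary outcome; chi-square is the one that fits a binary response.
- **Prognosis.** The Background says of severe disease that "the recurrence rate of postoperative adhesion can still be as high as 62.5" per cent, and the Discussion also describes severe disease as doing worse.

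**The concern.** Severity is recorded for every patient before allocation, and the endpoint is built from the same score. By Table 1, any residual adhesion scores at least 1 (extent) + 1 (type) = 2. A patient who starts at 5 must finish at 1 or less, so she responds only if the adhesions clear completely and menstruation is normal. A patient who starts at 12 need only reach 8, for example by menstruation returning to normal (4 + 4 + 0) with extent and type unchanged. The same responder label thus asks for different things in the two strata.

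If the strata respond at different rates, a chance difference in severity mix between arms moves the crude rate difference, and between-stratum variation adds noise that an unadjusted test leaves in. At stake are a few points of power and some protection of the estimate in a single-centre trial of 200.

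**Working it through.** **1. The plan's own sample size.** Sample size states 83 per arm, one-sided α = 0.025, β = 0.2. For the scaffold arm, "we assume that the effective rate of uterine adhesion repair can reach 80" per cent. For control there is only a range: "the repair rate of Foley balloon placement was 47–71.67" per cent. A single control rate has to be back-solved, and 60% works:

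n = 2·p̄(1−p̄)·(z₀.₉₇₅ + z₀.₈₀)² / d² = 2 × 0.70 × 0.30 × (1.960 + 0.842)² / 0.20² = 82.4, rounded up to 83.

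So 60% against 80% is an assumption consistent with the stated n; the article does not state it. The analysis section says "Two-tailed tests were used for all statistical analyses", with P ≤ 0.05. Its critical value of 1.96 is the same as for one-sided 0.025, so the two sections do not conflict here.

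**2. Chance imbalance in severity.** Assume 50% severe (not given in the article) and simple randomisation. The SD of the between-arm difference in severe share is sqrt(2 × 0.5 × 0.5 / n).

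- n = 100 per arm: SD = 0.0707; P(difference ≥ 10 points) = 15.7%.
- n = 83 per arm: SD = 0.0776; P = 19.8%.

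If the strata differed by 40 points in response (an assumption), a 10-point imbalance would move the crude difference by 0.10 × 40 = 4 points, against an assumed effect of 20.

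**3. Power with and without stratifying the analysis.** Simulated trials, 83 per arm, 50% severe, simple randomisation, overall rates 60% and 80%, critical value 1.96. CMH is the Cochran–Mantel–Haenszel test stratified by moderate/severe.

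| Assumed response, severe/moderate: control; scaffold | Chi-square | CMH | Change (points) |
|---|---|---|---|
| 60/60%; 80/80% (not prognostic) | 81.4% | 81.0% | -0.4 |
| 50/70%; 72/88% (weaker) | 81.4% | 82.6% | +1.2 |
| 40/80%; 66/94% (strong) | 81.4% | 86.6% | +5.2 |
| 80/40%; 94/66% (strong, reversed) | 81.5% | 86.8% | +5.3 |

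The strong scenario implies severe-to-moderate odds ratios of (0.40/0.60)/(0.80/0.20) = 0.17 in control and (0.66/0.34)/(0.94/0.06) = 0.12 with the scaffold.

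A second set with a common odds ratio, also at 50% severe, gives these changes from chi-square to CMH:

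- OR 0.5: 81.3% to 81.7%.
- OR 0.33: 81.4% to 83.2%.
- OR 0.2: 81.5% to 85.3%.
- OR 0.1: 81.2% to 88.4%, about +7. With 30% severe it is 81.4% to 89.7%, about +8.

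**4. Does stratified allocation add much?** At 50% severe, CMH power under stratified instead of simple randomisation is 83.4% against 83.2% at OR 0.33, and 89.0% against 88.4% at OR 0.1. Nearly all the gain comes from the analysis.

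**5. Validity.** With no treatment effect and simple randomisation, the unadjusted test rejects in the upper tail at 0.024–0.025, its nominal level. If allocation were stratified and the test left unadjusted, it would become conservative (0.021 at OR 0.33, 0.011 at OR 0.1), while CMH stays at 0.024–0.025.

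**The case against.** **The current test is not wrong.** This stands. Under simple randomisation the chi-square test holds its error rate, and that rate already allows for chance imbalance.

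**The point rests on silence.** This stands in part. The article condenses a fuller protocol, and covariate adjustment is commonly left to a statistical analysis plan, which is not shown. The analysis section does, however, list unadjusted tests by data type, and the randomisation section describes the sequence without a stratum.

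**Severity may not be strongly prognostic.** A reader might put the 62.5% beside the 71.67% and infer a large gap. The documents do not support that. The first is recurrence after surgery in severe disease. The second is an overall effective rate for the balloon, not tied to moderate disease. They are different outcomes from different cited sources, and support only a qualitative statement that severe disease does worse.

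**The direction is uncertain on this endpoint.** This also stands. Severe disease has the worse prognosis but more room for a 4-point fall, and the two may partly cancel. That limits the likely gain. It does not argue against stratifying, because the reversed scenario gains just as much and the null scenario loses only about 0.4 points.

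**The change is not free.** This stands. The article says the allocation sequence was registered, so re-preparing envelopes alters a registered sequence. Researchers also learn the allocation after surgery, so a change of primary test needs a documented reason and date.

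**Conclusion.** The point holds as an efficiency improvement. Baseline severity is known before allocation and enters the responder definition, yet the listed tests ignore it. At 83 per arm, 60% against 80% and half the patients severe, a stratified test changes power by about -0.4 points (severity not prognostic), +1 (weakly prognostic) or +5 to +7 (strongly prognostic), in either direction of prognosis. Without stratification, a severe-share difference of 10 points or more arises in about 16% of trials at 100 per arm.

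All of this rests on assumed inputs: the 60% control rate, the severe share and the stratum response rates. Two stronger readings should be resisted: that adjustment is certain to raise power at no cost, and that the chi-square result would be biased or invalid. The documents support neither. The unstated control rate matters far more to power: at 83 per arm, power runs from 99.6% at 47% control response to 24% at 71.67%.

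**What to change.** Before any unblinded analysis, specify the primary test as Cochran–Mantel–Haenszel, stratified by moderate/severe AFS as scored at the index procedure. Report a Mantel–Haenszel risk difference with 95% CI. This keeps the result on the response-rate scale that the article defines, which an adjusted odds ratio would not. The crude chi-square can be kept as a sensitivity analysis.

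The cost is a dated, justified change of analysis and a power loss of about 0.4 points if severity turns out not to be prognostic. No new data are needed.

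Stratifying envelopes not yet issued (separate moderate and severe series) is optional. It adds little beyond the analysis and means amending a registered sequence. If it is done, the stratified test must go with it.

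As a secondary suggestion, endometrial thickness could be analysed by ANCOVA on the screening value. The gain is unknown: screening thickness is measured shortly after menstruation and transfer-cycle thickness under exogenous estrogen, and a thin endometrium is an entry criterion, which narrows the baseline range.

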### Outcome measures

#### Primary outcome measures

The response rate of the repair of moderate/severe IUAs served as the main evaluation index.

The definition of an “effective repair of IUA” was considered as the total AFS of adhesion having been decreased by ≥4 points.

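### Pregnancy outcomes are compared by a valid but unadjusted chi-square test; adjusting for age and baseline AFS grade, both known before allocation, would be nearly free and could add a little precision

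*Protocol article*

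**What the plan says.** The *Statistical analysis methods* section assigns tests by type of variable. For outcomes such as pregnancy yes/no, "the chi-square test was used for nominal categorical variables". It adds that "Two-tailed tests were used for all statistical analyses", at the 0.05 level. No regression model and no covariate is named.

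Pregnancy is a secondary outcome. Of the secondary measures the article says "These included the endometrial thickness, menstrual volume, and clinical pregnancy rate", while for the primary outcome "The response rate of the repair of moderate/severe IUAs served as the main evaluation index". The rate is defined per transfer cycle: "Clinical pregnancy rate = the number of clinical pregnancies/the number of embryo transfer cycles × 100" per cent. Ongoing pregnancy has the same denominator.

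Two baseline characteristics are known before allocation:

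- **Age** is an inclusion criterion, with an upper limit of 40 years.
- **AFS grade** is scored in theatre: "Once the hysteroscopic process entered the uterine cavity, the degree of uterine cavity adhesion was evaluated according to AFS". The envelope is opened only after that, and only for moderate or severe disease.

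Allocation is 1:1 with no strata named. On prognosis, the *Background* says of severe adhesions that "the success rate of pregnancy will range between only 22.5 and 33.3" per cent.

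**The concern.** Improving pregnancy outcome is a declared aim of the trial, yet the sample size rests on adhesion repair alone. The article itself links severity to poor pregnancy prospects and enrols moderate and severe cases together. As written, neither the allocation nor the analysis uses severity or age. If these factors predict pregnancy, an analysis that ignores them leaves avoidable noise in the comparison. It also leaves the estimate exposed to whatever imbalance happens to arise. Fixing the covariates in advance would remove the temptation to adjust only after an imbalance has been seen.

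What is at stake is the precision of a secondary comparison. The type I error rate is not in question.

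**Working it through.** **The plan's own figures.** The article states no effect size, sample size or power for pregnancy, so there is no figure to reproduce for this comparison. Its 83 per arm is for the repair rate. The control rate there is given only as a range, 47–71.67%, so 83 does not follow from the stated inputs alone. With an assumed control rate of 60% against 80%, the pooled formula gives 82. The one number carried forward is 100 enrolled per arm less 20% dropout: 100 × 0.80 = 80.

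**Assumptions not in the document**

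- Control pregnancy rate 28%, close to the midpoint of the severe-only range: (22.5 + 33.3)/2 = 27.9. It is applied here to a mixed population.
- Experimental rate 48%, a gain of 20 points.
- Half of the women severe.
- 80 women per arm, each with one outcome.
- A range of prognostic strengths, shown in the table below.

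**Unadjusted power by formula** (two-sided 0.05)

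- Mean rate (0.28 + 0.48)/2 = 0.38.
- SE under the null: √(2 × 0.38 × 0.62/80) = 0.0767.
- SE under the alternative: √(0.28 × 0.72/80 + 0.48 × 0.52/80) = 0.0751.
- Power = Φ[(0.20 − 1.96 × 0.0767)/0.0751] = Φ(0.66) ≈ 0.745.

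**Simulation**, 3,000 trials per cell. The unadjusted chi-square is set against the test of the arm coefficient in a logistic model with age and severity. The variance ratio compares the standardised risk difference (adjusted) with the raw difference, under the alternative.

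| Odds ratio per SD of age; severe v moderate | Null rejection, unadjusted / adjusted | Power, unadjusted / adjusted | Gain (points) | Variance ratio |
|---|---|---|---|---|
| 1.0; 1.0 | 5.4% / 5.3% | 73.2% / 73.3% | 0.1 | 1.02 |
| 0.8; 0.7 | 4.9% / 5.0% | 71.4% / 72.4% | 1.0 | 0.99 |
| 0.7; 0.5 | 5.4% / 4.4% | 73.7% / 77.3% | 3.6 | 0.96 |
| 0.6; 0.4 | 5.8% / 5.3% | 74.6% / 79.4% | 4.8 | 0.91 |

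The simulation error of a null rejection rate is √(0.05 × 0.95/3000) ≈ 0.4 points. Both tests are therefore near 5%; the largest of the eight values is about two standard errors above it.

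A variance ratio of 0.91 is worth 80/0.91 ≈ 88 women per arm, or about eight extra per arm. At the other end, covariates with no prognostic value cost about 2% of variance.

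**Second parameterisation**, 6,000 trials per scenario: age SD about 4 years truncated at 40, odds ratio 0.90–0.95 per year, control pregnancy 28% in severe and 28–50% in moderate disease. At 80 per arm, power moves from 75.7% to 76.7%, from 72.2% to 75.9% and from 72.1% to 76.8% in three scenarios. At 60 per arm the change is −0.1 to +2.2 points.

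**Chance imbalance.** With 100 per arm and half severe, the SD of the difference in severe share is √(0.5 × 0.5 × 2/100) = 0.0707. A gap of more than 10 points therefore has probability 2[1 − Φ(0.10/0.0707)] ≈ 16%. If moderate cases conceive at 40–50% against 28% in severe cases, a 10-point gap shifts the raw difference by 0.10 × 12 = 1.2 to 0.10 × 22 = 2.2 points. The standard error is about 7.5 points, so the shift is at most 2.2/7.5 ≈ 0.3 of one standard error.

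**The case against.** The strongest reply is that nothing in the section is wrong. Under 1:1 allocation with no strata named, the unadjusted chi-square is a valid test, its error rate already allows for chance imbalance, and no stratification factor is ignored. This stands in full. A reader might infer that uncorrected imbalance biases or invalidates the pregnancy comparison; the null rejection rates above do not support that.

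The benefit also cannot be established from the document. It gives no effect of age on pregnancy, and its 22.5–33.3% is for severe disease only, with no moderate rate beside it. A flat statement that precision is being lost would go too far. Nor does the document support calling the pregnancy comparison underpowered, since it states no target effect for it.

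Two further points need care. The simulated power is for the arm coefficient of the logistic model. For the standardised risk difference recommended below, the relevant figure is the variance ratio. Also, pregnancies are counted per transfer cycle. A logistic model fitted to cycles would treat repeated cycles from one woman as independent, just as the chi-square does, and would leave out women who never reach transfer. Adding covariates repairs neither problem, so the adjustment makes sense only with one outcome per woman.

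Finally, covariate adjustment is often left to a statistical analysis plan, which is not shown. That would answer a complaint about silence. Here the article does state a test for this type of outcome, and a stated choice can be improved.

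**Conclusion.** The point holds as an optional efficiency improvement. The stated test is valid but ignores two baseline variables that are already recorded before allocation. Under the assumptions of 28% v 48%, 80 women per arm, half severe and one outcome per woman, adjustment gains about 0 to 5 points of power, with a variance change between +2% and −9%. Where in that range the trial lies depends entirely on the prognostic strength of age and AFS grade, which the document does not give. The gain may be nil. The outcome is secondary, and the point does not touch the primary conclusion or the type I error rate.

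**What to change.** In *Statistical analysis methods*, prespecify for clinical and ongoing pregnancy a logistic regression with one outcome per randomised woman, on arm, age (continuous) and baseline AFS grade (moderate or severe). Report the standardised risk difference with its 95% confidence interval. The text should say how a woman with several transfers, or with none, is counted. Keep the raw rates, including the per-cycle rates in *Secondary outcome measures*, as description. Leave out of the model anything settled after allocation, such as the number or stage of embryos transferred.

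The cost is a change of wording and one extra model, with no new data and no new participants. The downside is a variance increase of about 2% if neither covariate turns out to be prognostic.
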